### Study Objectives

The overarching goal of this investigation is to generate data that offer new knowledge that can be used to improve current clinical practice guidelines and develop new prescription algorithms for prosthetic ankle-foot devices. This information will lead to clinical prescriptions that facilitate the achievement of maximal functional ability and user satisfaction. Criteria will be developed to assist the limb loss care teams in prescribing appropriate, advanced prosthetic ankle-foot devices based on patient-specific needs and goals, in addition to the individual’s current physical abilities. Therefore, the purpose of this investigation is to develop the criteria for prosthetic ankle-foot prescription for veterans and service members with transtibial limb loss. The objectives of this investigation are as follows:

To determine the appropriate functional and biomechanical outcome measures to support the prescription of a type or category of prosthetic ankle-foot device for veterans or service members with transtibial limb lossTo correlate patient goals and subjective measures with objective data to determine the appropriate prosthetic ankle-foot category that will facilitate the greatest overall function for the userTo develop criteria for the appropriate prescription of nonarticulating ESR, ART, and powered plantarflexion ESR ankle-foot devices

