#### Visit 1—Screening, Consent, Enrollment, and Prosthetic Socket Assessment

Participants (N=100) will be recruited from the rehabilitation and prosthetics clinics at each site. The principal investigator, site–principal investigator, research assistant, research physical therapist, or study prosthetist will meet with interested patients to discuss the investigation and obtain informed consent. Once informed consent has been obtained, participants will be screened according to the inclusion and exclusion criteria and enrolled. Demographic information will be collected, including age, sex, race, ethnicity, height, weight, limb loss etiology, employment, marital status, living situation, and time since transtibial limb loss. A baseline pain measurement using a visual analog scale (VAS) of 0 (no pain) to 100 (worst possible pain) will be performed at the first visit. Fit and comfort of each participant’s existing socket will be evaluated by the study prosthetist using standardized prosthetic guidelines. Once fit and comfort are confirmed, the study prosthetist will create a mold using plaster of Paris or alginate to fabricate 2 additional, identical prosthetic sockets. All sockets will be centrally fabricated at VANYHHS. Identical materials and prosthetic componentry used in the participant’s current socket will be used to create each additional socket to eliminate any variance in perceived weight or socket flexibility. Each additional socket will be aligned with a designated ankle-foot device according to the manufacturer’s specifications by the study prosthetist.

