#### Visits 3 to 5—Functional Assessment of ESR, ART, and PWR Ankle-Foot Devices

Visit 3 will begin after the 1-week acclimation period while using the first assigned ankle-foot device. Participants will complete the VAS pain scale and then a battery of outcome measures and surveys (outlined in the following sections). In addition, during visit 3, a subset of participants will also be randomized to undergo biomechanical gait analysis while using the first prosthesis (described in the following sections). Once visit 3 is completed, the participant will receive the second prosthesis according to the established randomization schedule, and the initial prosthesis will be returned to the study prosthetist. The participant will again complete a 1-week acclimation period. During visit 4, the participant will undergo the same pain scale and battery of outcome measures and surveys. The same subset of participants will also undergo biomechanical gait analysis using the second prosthesis. The third prosthesis will be issued at the end of visit 4, and the second prosthesis will be returned to the study prosthetist. Participants will receive the same 1-week acclimation and will complete the same pain scale and battery of outcome measures and surveys during visit 5. In addition, the same subset of participants will undergo biomechanical gait analysis while using the third prosthesis. For visits 3 to 5, a visit window of –2 to +2 days will be implemented.

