#### Functional and Subjective Outcome Measures

The functional and subjective outcome measures were selected to optimize relevance to the participant population, providers, and health care systems. These measures are commonly used in prosthetic clinics and represent critical information in the functional and subjective domains needed to develop guidelines for prescription. Following the completion of the investigation, the selected outcome measures will be statistically analyzed to determine which measures are the most sensitive to changes in device type. The battery of functional outcome measures and subjective surveys collected after each acclimation period will be administered by a local research team member. Functional outcome measures include the 6-Minute Walk Test, Timed-Up-and-Go, Four Square Step Test, Amputee Mobility Predictor, Stair Assessment Index, and Hill Assessment Index. Surveys include the Prosthesis Evaluation Questionnaire, Short Form-12, and Orthotics and Prosthetics Users Survey. These measures are described in Textbox 2.

Measures included in the study.

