### Statistical Analysis

Across the study population, outcomes will be assessed using descriptive statistics (ie, means and SEs) and compared between each ankle-foot device category. Inferential statistics for ordinal data will be conducted with a repeated-measures Friedman test (α=.05) and a Dunn post hoc test at 95% CI. To identify which measures are the most sensitive to changes in ankle-foot device type, a linear mixed effects model will be used. Separate models will be run for each type of measure (ie, subjective, functional, and biomechanical), and measures that have a significant association with device type in the presence of adjusting or control variables will be determined. In the case of significance, pair-wise comparisons will be tested for significance using linear contrasts with Tukey Honestly Significant Difference or by applying Bonferroni correction. The performance of each device in each test will be ranked, and the arithmetic mode will be used to determine which device is the most suitable for each participant. Adjusting or control variables in the model will include weight, height, etiology, time since limb loss, sex, race, functional level, and current ankle-foot device.

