### Development of Prediction Model

To develop evidence-based guidelines for the prescription of prosthetic ankle-foot devices, the goal of this investigation is to determine which factors and outcomes are the most predictive of optimal performance to meet patient goals. To do this, initial analyses will consist of bivariate cross-tabulations, performed using chi-square analyses. Variable selection for the multivariate model will be informed by these bivariate findings. Logistic regression will then be performed with participants’ preference of prosthesis regressed on each of several domains (eg, functional levels and outcomes, activity levels, and biomechanical parameters). The models will simultaneously control for multiple variables, and overall model predictive value will be assessed using the C-statistic. Domain-specific models (based on bivariate findings) and 1 parsimonious stepwise logistic regression model combining the domains will be created to determine whether each distinct component predicts optimal prescription outcome. Each domain-specific model will control for the identified confounding factors. The individual variables of each domain will be used as fixed predictors. Finally, stepwise multiple regression will be used to determine the factors and outcomes that represent the best predictors, which will be conducted through a series of domain-specific, forward regression models. The significant variables in the forward selection models will then be placed in a backward regression model. Significant variables from the backward regression will be considered as the strongest predictive factors and used to develop prosthetic prescription guidelines.

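### The guideline model does not separate predictors known before a device trial from those that exist only after the ART or PWR foot has been worn

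*Protocol article*

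**What the plan says.** **The aim.** Under Study Objectives, the criteria are meant to help care teams "in prescribing appropriate, advanced prosthetic ankle-foot devices based on patient-specific needs and goals", and also to take account of what the individual can physically do at present.

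**Before the study feet are fitted.** The Visit 1 section lists the background variables (its last item is cut short here): "Demographic information will be collected, including age, sex, race, ethnicity, height, weight, limb loss etiology, employment, marital status, living situation, and time since transtibial limb". The one self-reported measure scheduled for that visit is the pain scale: "A baseline pain measurement using a visual analog scale (VAS"). Eligibility requires at least modified independence on two FIM mobility items. Visit 2 repeats the pain VAS and then has the participant walk on every prosthesis during dynamic fitting.

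**The outcome battery.** Functional and Subjective Outcome Measures states that "The battery of functional outcome measures and subjective surveys collected after each acclimation period will be administered by a local research team member". The first occasion is fixed under Visits 3 to 5: "Visit 3 will begin after the 1-week acclimation period while using the first assigned ankle-foot device". Gait analysis in the subset of 30 takes place at the same visits. Step activity is recorded in the 30-day home period, on all three prostheses.

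**The model.** Development of Prediction Model has "preference of prosthesis regressed on each of several domains (eg, functional levels and outcomes, activity levels, and biomechanical parameters"). It then runs forward and backward selection, and the variables left at the end are used to write the guidelines. It does not say on which foot the scores were obtained.

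**The concern.** A prescribing rule can use only what is known when the foot is chosen. A patient who has worn only an ESR foot has no 6-minute walk distance on a powered foot and no gait record on an articulating one. If the selection procedure retains such variables, the model says that people tend to prefer the foot on which they did better. That may be true and of interest, but it gives no rule for a patient assessed on the current foot alone.

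The activity domain raises a second problem. The Visit 6 section bases preference on total activity time for each prosthesis. If activity from the same 30 days also enters as a predictor, part of the outcome is predicted from itself. The C-statistic would then look better than any rule usable in advance could achieve.

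**Working it through.** The plan gives no figure on this point to reproduce. The check sets the visit schedule against the predictor domains and then counts.

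**Step 1: when each type of predictor first exists**

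| Predictor | First collected | Known before a trial of ART or PWR? |
|---|---|---|
| Demographics, etiology, time since limb loss | Visit 1 | Yes |
| Pain VAS | Visits 1 and 2 | Yes |
| FIM, two mobility items | Eligibility | Yes, but only scores 6 or 7 are admitted |
| Six functional tests, three surveys | Visits 3 to 5 | Only the ESR-condition scores |
| Gait parameters (30 participants) | Visits 3 to 5 | Only the ESR-condition values |
| Step activity | 30-day home period, all three feet in hand | No |

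The ESR rows qualify because Ankle-Foot Categorization has participants use their own current device for that category.

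**Step 2: how the device-specific scores divide** (inputs: 100 participants, 30 in the gait subset, 3 devices, complete data assumed)

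- Batteries: 100 × 3 = 300. On the own ESR foot: 100 × 1 = 100. On ART or PWR: 100 × 2 = 200, so 200/300 = 2/3.
- Gait sessions: 30 × 3 = 90. On the own ESR foot: 30. On ART or PWR: 60, again 2/3.

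**Step 3: how clean the ESR score is as a baseline** (input: the randomization section, which uses each device order equally often)

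- Number of orders: 3! = 6.
- Orders starting with ESR: 2, so 2/6 = 33%, or about 33 of 100 participants.
- The remaining 4/6 = 67%, about 67 of 100, take the ESR battery after at least one week at home on ART or PWR.
- All participants have walked on every foot at the Visit 2 fitting, so no battery score at all precedes that exposure.

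**Step 4: circularity.** The only activity measurement scheduled is that of the 30-day home period. The same recording supplies activity time per prosthesis, on which preference is based. The overlap is partial: a closeout interview also assesses preference, and the article does not say which activity summary would be the predictor.

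**The case against.** Four points on the other side have weight.

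1. **Some measures do come first.** A reader might infer that nothing functional or self-reported precedes the study feet. That is too strong: FIM and pain VAS do. The statement holds for the outcome battery, gait and step data. The FIM check has little spread, since each item can take only two values.

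2. **Scores on the current foot are collected for everyone.** A reader might infer that the model rests on ART and PWR scores alone. The article does not say so. Its model section leaves the foot unspecified, and one third of the planned scores are on the participant's own foot. This stands, and it is why the fix needs no new data. Having ESR first in only 2 of 6 orders does not show carryover either. It is a reason to account for order, not evidence of bias.

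3. **Trialling feet may be part of prescribing.** The ESR Group justification says that patients in these systems often try many feet in usual care, and the battery is described as common in prosthetic clinics. Scores on a trialled foot can then be legitimate evidence. A reader might infer that the main objective is not met, but the documents do not support that. What remains is that such criteria apply only after the trial, and the article does not mark that limit.

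4. **The statistical analysis plan may settle it.** Which condition supplies each predictor is detail often left to that document, which is not shown. But the article does state the schedule, the predictor domains and the use of the surviving variables for guidelines. Read together, these admit predictors unavailable beforehand, including the whole activity domain.

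A reader might also infer that adjusting for "time since limb loss, sex, race, functional level, and current ankle-foot device" removes part of the device effect. That would require functional level to be taken from a score measured on study feet. The article does not say so, and a clinical classification is equally plausible.

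**Conclusion.** The concern holds in a limited form. No measure from the outcome battery, gait analysis or step monitoring is scheduled before the study feet are fitted. The guideline model then mixes predictors available before a device trial with those available only after one. By count, two thirds of the planned device-specific scores (200 of 300 batteries, 60 of 90 gait sessions) are of the second kind, as is all home-period activity. These counts assume complete data. They describe what the model admits and do not measure bias.

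The comparisons between devices are unaffected. What is limited is the use of the selected predictors as prescribing criteria for a patient who has only the current foot. The circularity applies to the extent that preference is defined by activity time and activity from the same period is a predictor.

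**What to change.** In Development of Prediction Model:

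1. Build the guideline model from visit 1 variables plus battery scores from the ESR condition. Gait values from the ESR condition can enter only for the subset of 30.
2. Adjust for device order, or check whether results differ between participants tested on ESR first and the rest.
3. Exclude 30-day activity as a predictor wherever preference is based on activity time.
4. Report models that use ART or PWR scores separately, labelled as explanatory or as applicable only once those feet have been trialled.

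This changes analysis wording only. It needs no new visit or measurement, and the Results section places full data analysis after final data collection. The price is fewer candidate predictors and probably a lower C-statistic, but one that describes what a prescriber could achieve with information in hand.

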#### Biomechanical Analysis

In addition to completing the functional and subjective outcome measures during visits 3 to 5, a subset of 30% (30/100) of the participants will also undergo gait analysis during these visits. Biomechanical gait analysis will include kinetic and kinematic evaluation of level ground walking at 3 speeds and kinematic evaluation of incline and decline ambulation at a self-selected speed. The purpose of these sessions is to collect joint angles, forces, torques, and powers while participants use each ankle-foot device.

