### Sample Size Determination and Power Analysis

Sample size determination was based on power analysis of several biomechanical, subjective, and functional measures collected during pilot investigations (Table 2). Assuming an α error rate of 5% and using within-group SDs determined from the pilot investigations, power is provided for selected parameters for a sample size of 100 participants for functional and subjective outcomes and a sample size of 30 for biomechanical parameters.

**Table 2 table2:** Sample size determination and power analysis of selected parameters.

Parameters		Difference, mean (SD)	Power (N=100; subset of 30/100, 30%, where appropriate), %

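### Significance after stepwise selection in 100 participants (30 with gait data) decides which predictors enter the prescription guidelines, a rule with a substantial chance of admitting noise

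*Protocol article*

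**What the plan says.** The section Development of Prediction Model sets out a sequence.

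- Screening: "initial analyses will consist of bivariate cross-tabulations, performed using chi-square analyses", and "Variable selection for the multivariate model will be informed by these bivariate findings".
- Modelling: the preferred prosthesis is regressed on several domains, with biomechanical parameters named as one of them. In addition, "1 parsimonious stepwise logistic regression model combining the domains will be created".
- Assessment: "overall model predictive value will be assessed using the C-statistic".
- Final selection: forward models are run domain by domain, and their significant variables go into a backward model.
- Use of the result: "Significant variables from the backward regression will be considered as the strongest predictive factors and used to develop prosthetic prescription guidelines".

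Gait data are limited. Under Biomechanical Analysis, "a subset of 30% (30/100) of the participants will also undergo gait analysis during these visits". The section Sample Size Determination and Power Analysis gives power for "a sample size of 100 participants for functional and subjective outcomes and a sample size of 30 for biomechanical parameters". That power concerns differences in selected outcome measures. The article gives no sample-size reasoning for the prediction model.

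**The concern.** Every step after data collection uses statistical significance in the same participants, and the last step turns whatever survives into guideline content. When there are many candidates and few participants per preferred device, some unrelated variables will pass by chance. A C-statistic computed on the data that chose them will then look better than the model performs in new patients.

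This is not a side analysis. The Objective and Study Objectives name prescription criteria as the purpose of the trial, and this procedure is what produces them. A false predictor would become advice on which foot to prescribe.

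**Working it through.** The article states no target C-statistic, events-per-candidate figure or sample size for this model, so there is no stated figure to reproduce. The check counts the candidates and then runs the described sequence on predictors that carry no information.

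**Candidates listed in the article**

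- Functional: 6 tests (Functional and Subjective Outcome Measures).
- Subjective: 9 Prosthesis Evaluation Questionnaire scales + Short Form-12 + Orthotics and Prosthetics Users Survey = 11, counting each of the last two once.
- Patient factors: 8 adjusting variables (Statistical Analysis) + pain score = 9.
- Gait: 5 temporal-spatial + 4 parameter types × 3 joints + 4 others = 21 (Data Analysis), before limb side, gait phase or the 3 speeds are counted.

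Without gait: 6 + 11 + 9 = 26. With gait: 26 + 21 = 47. If each measured outcome is entered once per device: 18 + 33 + 9 = 60 without gait, and 21 × 3 = 63 for gait alone.

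**Information available.** With three devices, the least-preferred one has at most 33 of 100 participants, or 10 of 30. Events per candidate are therefore at most 33/26 = 1.3 at N=100, 10/21 = 0.5 for gait alone, and 10/47 = 0.2 for all domains at N=30.

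**Simple bound.** For k independent noise candidates each tested at 0.05, the chance of at least one false signal is 1 − 0.95^k: 74% for k = 26, 91% for k = 47, 95% for k = 60.

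**Simulation of the sequence.** The steps were: chi-square screen on median splits; forward selection within each domain at p<0.05; backward elimination of the pooled survivors at p<0.05; apparent C; then C in 400 new participants. There were 400-600 replicates per setting. Assumed, because the article does not state them:

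- screening threshold 0.05, 0.20 or none;
- entry and removal level 0.05;
- within-domain correlation 0 or 0.5;
- share preferring the modelled device 33% (also 50% for the smaller candidate sets).

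Ranges run over these assumptions. The median apparent C is taken over trials in which something survived.

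| Setting | Candidates | Trials keeping at least one noise predictor | Median apparent C | C in new participants |
|---|---|---|---|---|
| N=100, no gait | 26 | 29-73% | 0.64-0.67 | 0.50 |
| N=100, no gait, per device | 60 | 52-96% | 0.67-0.74 | 0.50 |
| N=30, gait only | 21 | 21-70% | 0.75-0.83 | 0.50 |
| N=30, gait only, per device | 63 | 50-98% | 0.79-1.00 | 0.50 |
| N=30, all domains, complete cases | 47 | 45-92% | 0.78-0.88 | 0.50 |

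Optimism (apparent minus new-data C) is 0.14-0.17 in the first row (0.64 − 0.50 to 0.67 − 0.50) and 0.28-0.38 in the last (0.78 − 0.50 to 0.88 − 0.50).

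**The case against.** The strongest reply is that this is a condensed article. Internal validation, entry thresholds, the candidate list and missing-data handling are commonly left to a fuller plan, so a reader should not infer that the C-statistic will definitely go uncorrected. That stands. It does not remove the problem, because the published rule admits variables to the guideline on significance. Correcting C afterwards would lower the reported figure and leave the same variables in.

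Other stronger readings are tempting but go beyond the text:

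- *Noise is bound to look predictive.* It is a probability. With the strictest screen and few candidates, noise survives in a minority of trials, and at N=100 an apparent C near 0.65 is modest.
- *The combined model must shrink to 30 participants.* That assumes complete-case fitting, which is not stated. The final backward model would lose participants only if a gait variable reached it. The gait-only model has at most 30 in any case.
- *The model is wrongly binary for a three-way choice.* The article says only logistic regression; multinomial or one-device-versus-rest forms both fit that wording.
- *Continuous scores are forced into categories.* The article does not say which variables are cross-tabulated, and several (sex, race, etiology) are categorical already. The median split above is a device of the simulation.

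It is also fair to say that the device comparisons and the randomization do not depend on this model.

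**Conclusion.** The concern holds as a risk created by a rule the article fixes. Variables that stay significant after chi-square-informed screening, forward selection and backward selection in the same participants are declared the strongest predictors and passed to the guidelines. Even where nothing predicts preference, that rule yields at least one such factor in roughly 29-73% of trials in the 26-candidate setting at N=100, and in 45-92% with all 47 candidates at N=30 under complete-case fitting.

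The apparent C is misleading mainly at N=30. There the median model built on noise reaches 0.75 or more, which a reader would take for useful discrimination.

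The exact percentages depend on the assumed thresholds, preference split and correlations, and on treating all listed measures as candidates. Enrolment of 100 and 30 is also taken without attrition, which favours the plan. That new-data performance is no better than chance when nothing is related to preference does not depend on those assumptions.

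**What to change.** Before the prediction model is fitted, amend the analysis wording as follows.

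1. Drop significance after stepwise selection as the criterion for guideline predictors. Use a short predictor list fixed in advance, or a ridge- or lasso-penalised model.
2. Repeat the entire selection, screening included, inside a bootstrap. Report the optimism-corrected C-statistic together with calibration.
3. Fit the combined model on the domains measured in all participants.
4. Label the biomechanical model (n=30) exploratory, and do not draw guideline criteria from it directly.

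The choice among logistic forms for the three-device preference can stay with the trial statistician. No new data or visits are needed. The cost is plan wording and some programming, and the reported C-statistic will be lower.
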